### Exclusion criteria

Patients will be excluded if they have the following criteria:
Patients with other intestinal diseases (e.g., bacterial dysentery, intestinal tuberculosis, Crohn’s disease)Patients with serious complications (e.g., intestinal perforation, intestinal obstruction, toxic megacolon, colorectal cancer)Patients who are pregnant, breast-feeding, or preparing for pregnancyPatients with significant cardiac disease, hepatic disease, pulmonary disease, renal disease, and other serious diseases (abnormal urine protein, platelet value of less than 100 × 109/L, alanine aminotransferase level above the upper limit of normal, leukocyte count of less than 4.0 × 109/L)Patients who have severe physical disability (e.g., blindness, deafness, dumbness, intellectual disability, mental disability, physical disability)Patients who have a history of alcohol or drug abusePatients who have a history of food allergy or drug allergyPatients who are participating in other clinical trials

### Withdrawal criteria

Patients who *do not* meet the inclusion criteria, have no data after randomization, have never used research medication, and take forbidden drugs will be withdrawn from this study.

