**Methods:**

This is a multicenter, randomized, double-blind, placebo-controlled, superiority trial. A total of 120 patients with moderately active UC will be recruited from 10 hospitals in China. Each eligible participant will be randomly assigned to receive QCHS granule or placebo for 12 weeks. Both groups will be given basic treatment with mesalazine (4 g/day). The primary outcomes are the clinical response (remission) rate. The secondary outcomes are health-related quality of life, endoscopic response rate, mucosal healing rate, and inflammatory markers (e.g., fecal calprotectin and CRP). The whole study period will last 36 weeks, including 24 weeks follow-up time. According to the intention-to-treat principle, variables will be assessed at 2, 4, 6, 8, 10, and 12 weeks after study commencement.

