### Sample size and power calculation

The sample size was calculated according to the primary outcome (clinical response rate) at 12 weeks after initiation. The sample size calculation was based on the comparison of the proportions in the QCHS granule group versus the placebo group. On the basis of previous study and clinical experience, we predicted that the clinical remission rates at 12 weeks would be 79% in the QCHS granule group and 41% in the placebo group [27, 28]. A difference of 10% was selected as the smallest difference that would be of clinical significance. For a two-sided significance level of 0.05 (*α* = 0.05), it is estimated that a sample size of 54 subjects per group will be required to detect the superiority of QCHS granule over placebo with a test power of 80%. Under the hypothesis that some patients are unable to follow-up or unsuitable for analysis, the sample size will be inflated. Considering 10% drop out, the total planned sample size will be 60 per group.

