### Dropout criteria

Patients who are unable to be followed-up after informed consent and randomization will be considered dropout of our study.

Those patients who discontinue will be followed up for detailed reports throughout the study. We will try our best to contact subjects, record reasons, and complete assessment. Those patients who suffer an adverse event will be treated according to clinical practice guidelines. All the data of the research process will be recorded timely and accurately.

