### Statistical analysis

According to our protocol, all data analyses will be conducted based on pre-established statistical analysis plan. All analyses of data will be performed by SAS software (v. 9.3; SAS Institute Inc., Cary, NC, USA). To ensure the consistency and reliability of the conclusions, both intention-to-treat (ITT) analysis and per-protocol (PP) analysis will be done if necessary. All missing data will be imputed by multiple imputation. Statistical description will be performed with frequency, mean, median, standard deviation, lower quartile (P25), upper quartile (P75), minimum, and maximum. Normality of all quantitative (continuous) variables (e.g., demographic characteristics, vital signs, biochemical parameters) will be tested by the Kolmogorov-Smirnov test. For normal distribution data, independent sample *t* test and paired sample *t* test will be employed to compare parameters at the beginning and the end of the study between and within groups, respectively. For abnormal distributions data (e.g., quality of life, inflammation markers), the Mann-Whitney *U* test and Wilcoxon signed-rank test will be used instead. For qualitative (categorical) variables, the chi-square test or Fisher’s exact test will be used, such as clinical response rate, endoscopic response rate, and mucosal healing rate. In the evaluation of efficacy and analysis of influencing factors, center and disease will be used as covariates. Covariance analysis (ANCOVA) will be used [35]. Multiple linear regression or logistic regression will be used to analyze the influencing factors and evaluate the effect of gender and condition on the efficacy of the two groups. For all analyses, *P* < 0.05 will be considered statistically significant.

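### The withdrawal rule takes randomised patients out of the study for post-randomisation events, and it is not reconciled with the declared intention-to-treat principle, the continued follow-up or the multiple imputation

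*Protocol article*

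**What the plan says.** Five places in the protocol article bear on who is followed and who is analysed.

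- **Abstract, Methods:** "According to the intention-to-treat principle, variables will be assessed at 2, 4, 6, 8, 10, and 12 weeks after study commencement".
- **Withdrawal criteria:** besides patients who turn out not to meet the inclusion criteria, those who "have no data after randomization, have never used research medication, and take forbidden drugs will be withdrawn from this study". I read the listed grounds as alternatives, since a patient could hardly meet all of them at once.
- **Dropout criteria:** "Those patients who discontinue will be followed up for detailed reports throughout the study". The section adds that the team will try to reach patients and complete their assessments.
- **Statistical analysis:** "both intention-to-treat (ITT) analysis and per-protocol (PP) analysis will be done if necessary", and "All missing data will be imputed by multiple imputation". Neither analysis is named as primary.
- **Sample size and power calculation:** on the expectation that "some patients are unable to follow-up or unsuitable for analysis, the sample size will be inflated", 54 per group becomes 60.

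Withdrawal, dropout and termination are three separate headings, each with its own grounds.

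**The concern.** Under intention-to-treat, what happens to a patient after randomisation does not decide whether that patient counts. Three of the withdrawal grounds are post-randomisation events, and the rule takes the patient out of the study.

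Forbidden-drug use is the ground that matters most. The article does not list the forbidden drugs, so a link with treatment failure is an inference. It is a reasonable one, because the trial enrols patients who have not responded to 5-ASA, and the Background names other drugs recommended for inducing remission. If patients who are doing badly are the ones who take such drugs, the rule selects on something close to the outcome, and possibly at different rates in the two arms.

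The other grounds are weaker. Failing the inclusion criteria is settled before randomisation, and never taking a blinded study drug is less likely to differ by arm.

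At stake is whether the week-12 comparison is one of the groups as randomised. An outcome never collected because the patient left cannot be collected later.

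**Working it through.** **Step 1. Two readings of withdrawal.**

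*(a) Left out of the analysis.* A patient withdrawn for having no data has little left to be removed from except the analysis. The sample size section also expects some patients to be unsuitable for analysis. On this reading the analysed set is not the randomised set.

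*(b) Leaves the study but stays in the analysis.* The Outcomes section bases response on the total Mayo score. Under Data collecting and follow-up, the Mayo score and colonoscopy are taken at the beginning and end, and visits from week 2 to week 10 collect only the partial score. A patient who leaves before week 12 therefore has no primary outcome, and it must be imputed.

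**Step 2. Inputs.**

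- Planned rates at week 12, from the sample size section: "would be 79% in the QCHS granule group and 41% in the placebo group", a difference of 38 points.
- Group size: 54/(1 − 0.10) = 60, as the article states. The 10% allowance is 0.10 × 60 = 6 patients per arm. How 54 was derived does not matter here.
- Smallest clinically relevant difference, from the same section: 10 points.
- Test level: "For a two-sided significance level of 0.05".
- Assumed, with no source in the document: the number withdrawn in each arm, and that all of them are non-responders. The second assumption is the extreme case.

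**Step 3. One arm loses 6 non-responders.** Apparent rate = (rate × 60)/(60 − removed).

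- At 41%: 24.6/54 = 45.6%, up 4.6 points.
- At 79%: 47.4/54 = 87.8%, up 8.8 points.

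**Step 4. Both arms lose patients.**

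| Removed, QCHS / placebo | QCHS | Placebo | Difference |
|---|---|---|---|
| 0 / 0 | 79.0% | 41.0% | 38.0 |
| 6 / 6 | 47.4/54 = 87.8% | 24.6/54 = 45.6% | 42.2 |
| 4 / 10 | 47.4/56 = 84.6% | 24.6/50 = 49.2% | 35.4 |

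The difference can move either way. In the last row it moves 2.6 points against QCHS.

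**Step 5. No true effect, 41% in both arms.** Apparent rate = 0.41/(1 − share removed). The error rates come from 200,000 simulated trials of 60 per arm with a pooled z-test.

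| Share removed | Apparent rates | Spurious difference | Type I error |
|---|---|---|---|
| 10% and 10% | 45.6%, 45.6% | 0 | about 5% |
| 10% and 20% | 45.6%, 51.2% | 5.7 points | about 9% |
| 5% and 20% | 43.2%, 51.2% | 8.1 points | about 13% |

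The spurious difference favours whichever arm loses more patients. With all randomised patients analysed and their true outcomes known, the error stays at about 5% in every row.

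**Step 6. Does imputation remove this?** Not by itself. An imputation using only the treatment arm fills in each missing outcome at the arm's observed rate. For placebo with 6 missing, (24.6 + 6 × 0.456)/60 = 45.6%, the same as deletion. A model that also uses interim partial Mayo scores or forbidden-drug use would do better, by an amount the article does not allow one to calculate.

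**The case against.** The strongest reply is that the article never says withdrawn patients leave the analysis. It says they leave the study, and in the Statistical analysis section it imputes all missing data. The follow-up sentence under Dropout criteria, placed after dropouts are defined as people who cannot be followed, reads naturally as covering anyone who discontinues. On that view the patients are followed, imputed where needed and analysed. The article also defers to a statistical analysis plan that is not shown, where analysis sets are commonly defined.

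Much of this stands. A reader might infer that exclusion from analysis is settled; it is an inference from the wording. A reader might also infer that ITT alone is optional, but the conditional phrase covers ITT and per-protocol together. The absence of detailed set definitions is not the point here.

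The contradiction remains. A patient cannot be both withdrawn from the study and followed throughout it, and the article does not say which statement prevails. Imputation answers reading (a) only by moving the problem to reading (b), where a collectable outcome is replaced by a modelled one.

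**Conclusion.** The point holds as a conflict within the article: the withdrawal rule is not reconciled with the intention-to-treat principle, the follow-up promise or the imputation sentence, and the conditional phrase leaves neither analysis firmly committed. On either reading of withdrawal the primary comparison can be biased.

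The size and direction are unknown. The shifts of about 5 and 9 points in a single arm, and the change from 38 to about 35 points in the difference, rest on assumed counts and on every removed patient being a non-responder. They show that the effect could be material against a relevant difference of 10 points; they are not predictions.

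Two stronger readings are not supported. One is that the rule does bias the trial, or does so in favour of QCHS: equal removal under no effect gives no spurious difference, and heavier loss of placebo failures works against QCHS. The other is that the damage could never be examined: the randomisation list would still allow all-randomised, non-response and worst-case analyses, although the missing week-12 scores themselves would stay missing.

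**What to change.** Reconcile the Abstract, Withdrawal criteria, Dropout criteria and Statistical analysis sections on data retention.

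1. In Withdrawal criteria, state for example: All randomised patients, including those who meet any ground listed here, remain in follow-up for the week-12 assessment where possible and are included, in the group to which they were randomised, in the primary analysis. The listed grounds define only the per-protocol set.
2. In Statistical analysis, delete the conditional phrase, name the analysis of all randomised patients as primary and keep per-protocol as a sensitivity analysis.
3. Before unblinding, prespecify how outcomes after forbidden-drug use are handled. Counting them as non-response is one option; using the observed week-12 outcome is another. State what multiple imputation is reserved for.

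This concerns follow-up and analysis only and proposes no rule on stopping treatment.

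The cost is a wording amendment plus the effort of obtaining week-12 assessments, including colonoscopy, in patients who would otherwise have left. Trial status reports that enrolment began in April 2016 and is still open, so the change can cover patients yet to reach week 12. Week-12 colonoscopies already missed cannot be retrieved, and those patients will need the prespecified missing-data handling.

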### Dropout criteria

Patients who are unable to be followed-up after informed consent and randomization will be considered dropout of our study.

Those patients who discontinue will be followed up for detailed reports throughout the study. We will try our best to contact subjects, record reasons, and complete assessment. Those patients who suffer an adverse event will be treated according to clinical practice guidelines. All the data of the research process will be recorded timely and accurately.

### Termination criteria

Patients will be terminated if they meet the following criteria:
Abnormality of safety index during treatment (ALT more than twice the upper limit of normal, Cr more than the upper limit of normal, platelet count less than 50 × 109/L, white blood cells less than 3.0 × 109/L)Worse condition during the course (bloody stools more than 6 times daily accompanied by body temperature > 37.8 °C or Hb < 10.5 g/dL)

### Intervention

#### Basic treatment

During the intervention period, all eligible patients with moderately active UC will receive standard treatment of Mesalazine Sustained Release Granules (5-aminosalicylic acid, 5-ASA, 4 g daily) produced by French IPSEN Pharmaceutical Factory.

#### QCHS granule group

Those patients randomized to the intervention group will receive Qing-Chang-Hua-Shi granule (QCHS, 125 g daily, orally) additionally. This Chinese herbal prescription consists of several ingredients: Rhizoma Coptidis (Huanglian) 6 g, Radix Scutellariae (Huangqin) 10 g, Herba Patriniae (Baijiangcao) 15 g, Angelicae Sinensis Radix (Danggui) 10 g, Radix Paeoniae Alba (Baishao) 20 g, Radix Angelicae Dahuricae (Baizhi) 12 g, Radix Aucklandiae (Muxiang)6 g, Radix Sanguisorbae (Diyu) 10 g, Lithospermum Erythrorhizon (Zicao) 10 g, Rubia Cordifolia (Qiancao) 20 g, and Licorice (Gancao) 6 g.

#### Control group

Patients in the control group will be treated with 5-ASA plus QCHS granule placebo (125 g daily, orally). QCHS granule placebo is similar to QCHS granule in terms of appearance, size, color, smell, taste, doses, and containers. Furthermore, the composition of the placebo is starch, maltodextrin, caramel pigment, tartrazine pigment, sugar octoacetate, amaranth, and lactose.

According to the Good Agricultural Practice (GAP), all ingredients of Chinese herbal granule and placebo were manufactured by Jiangyin Tianjiang Pharmaceutical Co., Ltd., Jiangyin, China. Raw herbs were extracted in hot water, and the aqueous extract was concentrated, dried, and packed in sealed opaque packages. According to the theory of Chinese medicine, the patient should take half of the decoction in the morning and half in the evening. Instruction and code label will be tagged outside the container. Participants were asked to dissolve the granules by hot water and drink the mixture.

### Study period

The total course of intervention is 12 weeks with 24 weeks follow-up. After enrollment, the trial will last 36 weeks continuously.

### Outcomes

The primary outcome of this study is the clinical response rate in patients with moderately active UC. The clinical response refers to a decrease (from the baseline) of the total Mayo score by at least 30% (or 3 points) together with a decrease of the rectal bleeding subscore by at least 1 point (or rectal bleeding subscore of 0 or 1 point) with no individual subscore exceeding 1 point [32].

The secondary outcomes are as follows: health-related quality of life measured by the Inflammatory Bowel Disease Questionnaire (IBDQ) [33], endoscopic response rate defined as a decrease of Mayo disease activity index endoscopy subscore by at least 1 [32], mucosal healing rate defined as endoscopy subscore of Mayo disease activity index of 0 or 1, and improvements in inflammatory markers (e.g., fecal calprotectin, tumor necrosis factor-α and hypersensitive-C reactive protein, erythrocyte sedimentation rate) [34].

### Additional information

In addition, information regarding biological index (e.g., demographic characteristics, vital signs) and diagnostic index (e.g., course, status, physiological and biochemical indicators) will be obtained at baseline and follow-up. Safety index will be observed throughout the study. During the study, adverse events (AEs), such as liver dysfunction, renal dysfunction, electrocardiographic abnormality, urine protein, urine leukocyte, bloody stools, and infection, will be recorded on a standard SAE form. Those patients who experienced SAEs will be followed up for detailed reports and reported to the Institutional Review Board (IRB) of the Affiliated Hospital of Nanjing University of Chinese Medicine as required indicating expectedness, seriousness, severity, and causality.

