## Hypothesis and objective

In our protocol, we hypothesize that QCHS granule combined with basic treatment (5-ASA) is superior to placebo plus 5-ASA on clinical response (remission) rate, mucosal healing rate, clinical syndromes, quality of life, inflammatory mediators (e.g., fecal calprotectin, TNF-α, and hs-CRP), and adverse side-effects.

The primary objective of this trial is to investigate the efficacy of QCHS granule combined with 5-ASA in the management of patients with moderately active UC. Furthermore, the secondary objective is to explore the safety of QCHS granule for moderately active UC.

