### Data collecting and follow-up

According to the protocol, assessments will be repeated 7 times during the 12 weeks intervention: at baseline, at 2 weeks, at 4 weeks, at 6 weeks, at 8 weeks, at 10 weeks, and at 12 weeks. For those patients who have been induced to remission at the end of the intervention, we will follow up for 24 weeks. After enrollment, participants will attend a total of thirteen trial visits. Participants who completed our trial will be provided with 400 RMB for transport compensation. At the beginning and the end of the study, Mayo score, colonoscopy, mucosal histology, heath-related quality of life, biochemical parameters, and safety index will be measured. However, partial Mayo score, symptom indicators (e.g., diarrhea, bloody stools, and abdominal pain), biochemical parameters (e.g., fecal calprotectin, hypersensitive-C reactive protein, erythrocyte sedimentation rate, stool routine, occult blood test), and safety index (e.g., blood routine, liver function and kidney function) will be evaluated at 2 weeks, 4 weeks, 6 weeks, 8 weeks, and 10 weeks respectively.

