## Discussion

UC is a chronic immune-mediated (nonspecific) inflammatory condition. Patients with active UC are more likely to have comorbid psychological conditions of anxiety and depression, resulting in impaired social interactions or career progression [36]. As a difficult and incurable disease, the optimal goal of its management is to induce (steroid-free) remission, maintain remission (especially mucosal healing), and prevent disease-related complication and health-related quality of life [12]. Therapeutic options in patients with moderately active UC include 5-aminosalicylic acid, corticosteroids, and anti-TNF therapy (e.g., adalimumab, golimumab, and infliximab). In our clinical practice, many patients do not respond to these conventional drugs. As a result, strategies for the management of moderately active UC mainly depend on the following factors: the risk and benefit of the choice, preference of the patients, and experience of the doctors. The use of TCM in patients with moderately active UC has increased in popularity over the past decade because of the unique advantages of efficacy, convenience, safety, and low cost [18]. In Asian countries, especially in China, Korea, and Japan, herbal medicines have been widely used for approximately 2000 years to treat and manage UC-like symptoms, such as diarrhea, abdominal pain, and mucus/bloody stool. Qing-Chang-Hua-Shi granule (QCHS) is a classical Chinese herbal formula, which is composed of Huanglian, Huangqin, Baijiangcao, Danggui, Baishao, Diyu, Zicao, Qiancao, Baizhi, Muxiang, and Gancao herbs. Our previous studies have proved that QCHS could alleviate UC oxidative stress and intestinal inflammation which was related to activation of β2AR/β-arrestin2/NF-κB signaling pathway [37]. Moreover, an in-depth study found paeoniflorin had the anti-inflammatory effect in UC via inhibiting MAPK/NF-kappa B pathway and apoptosis in mice [38], and astragalus and baicalein regulated inflammation of mesenchymal stem cells by MAPK/ERK pathway [39]. Based on the abovementioned results, we explored whether QCHS could help patients with moderately active UC who do not respond to 5-ASA after 4 weeks. To the best of our knowledge, this is the first prospective, multicenter, randomized, double-blind, placebo-controlled, superiority clinical study protocol regarding Chinese herbal extract granules in the management of moderately active ulcerative colitis. Furthermore, our protocol is strictly developed according to the requirements of SPIRIT 2013 statement and SPIRIT-TCM extension 2018 statement. We hypothesize that QCHS granule combined with basic treatment (5-ASA) is superior to placebo plus 5-ASA on clinical response (remission) rate, mucosal healing rate, clinical syndromes, and quality of life. As a result, our study will be conducted by a group of experienced experts from 10 subcenters (tertiary hospitals) across China. Interactive Web Response System (IWRS) will be used throughout the study. It is inevitable that we need to control the quality of our research. If the trial shows significant benefits of QCHS granules, there is evidence that we can prescribe QCHS granule combined with 5-ASA for moderately active ulcerative colitis in the clinical practice.

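### Superiority is hypothesised on adverse side-effects while bloody stools, also an efficacy sign, counts as an adverse event, so an overall adverse-event comparison could favour QCHS through efficacy alone

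*Protocol article*

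**What the plan says.** All references are to the protocol article.

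- **Hypothesis and objective.** The list of outcomes on which QCHS plus 5-ASA is expected to be superior ends with "inflammatory mediators (e.g., fecal calprotectin, TNF-α, and hs-CRP), and adverse side-effects". The same section adds that "the secondary objective is to explore the safety of QCHS granule for moderately active UC".
- **Additional information.** The adverse events given as examples are liver and renal dysfunction, ECG abnormality, and then "urine protein, urine leukocyte, bloody stools, and infection, will be recorded on a standard SAE form". Nothing restricts the bloody-stools item to bleeding that is new or worse than at baseline.
- **Outcomes.** The primary response requires, besides the fall in total Mayo score, "a decrease of the rectal bleeding subscore by at least 1 point" or a low absolute bleeding subscore.
- **Data collecting and follow-up.** Between baseline and week 12 the visits record "symptom indicators (e.g., diarrhea, bloody stools, and abdominal pain", together with blood, liver and kidney tests as a safety index.
- **Termination criteria.** Disease worsening is described as "bloody stools more than 6 times daily accompanied by body temperature > 37.8 °C or Hb < 10.5 g/dL".
- **Statistical analysis.** Categorical variables are compared by chi-square or Fisher's exact test, and P < 0.05 counts as significant for every analysis. No adverse-event comparison is named.
- **Discussion.** The hypothesis is restated as "superior to placebo plus 5-ASA on clinical response (remission) rate, mucosal healing rate, clinical syndromes, and quality of life", with no mention of adverse effects.

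**The concern.** One clinical sign serves as a component of the primary outcome, a symptom measure, a marker of worsening and an adverse event. Patients enter with active UC, so bleeding is a feature of the disease under treatment. If QCHS reduces bleeding, fewer QCHS patients may have a bloody-stools event recorded, whatever else the product does. On its own that is ordinary safety recording. It becomes a problem because the plan also hypothesises superiority on adverse side-effects and applies a significance rule to all categorical comparisons. An overall adverse-event rate tested in that way could look better for QCHS because of efficacy. It could also make an excess of other events look smaller than it is. Safety is the stated secondary objective.

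**Working it through.** The article gives no adverse-event rate, so there is no planned figure to reproduce. What follows is an illustration.

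**Inputs from the article** (Sample size and power calculation): 79% v 41% at 12 weeks, 60 per group, two-sided 0.05. That section sizes the trial on clinical response but calls these two figures remission rates; they are used here as response rates. Non-response is then 1 − 0.79 = 0.21 for QCHS and 1 − 0.41 = 0.59 for placebo.

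**Assumptions, none from the article:**
- A share *q* of non-responders has a bloody-stools event recorded, and responders have none.
- Other adverse events occur at rate *h*, independently of bleeding.

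**Formula:** any-event rate = 1 − (1 − *q* × non-response)(1 − *h*).

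**Case A: other events truly doubled, 10% (QCHS) v 5% (placebo).**
- *q* = 0.10: 1 − 0.979 × 0.90 = 11.9% v 1 − 0.941 × 0.95 = 10.6%. The excess is still visible, but shrinks from 5 points to about 1.
- *q* = 0.25: 1 − 0.9475 × 0.90 = 14.7% v 1 − 0.8525 × 0.95 = 19.0%. The direction is reversed.
- *q* = 0.50: 1 − 0.895 × 0.90 = 19.5% v 1 − 0.705 × 0.95 = 33.0%. The direction is reversed; in 60 per group this is about 12 v 20 patients.

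The break-even share solves 0.90(1 − 0.21*q*) = 0.95(1 − 0.59*q*), so 0.3715*q* = 0.05 and *q* ≈ 0.13.

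**Case B: other events 30% v 20%.** The rates are 31.5% v 24.7% (*q* = 0.10), 33.7% v 31.8% (*q* = 0.25) and 37.4% v 43.6% (*q* = 0.50). Break-even: 0.70(1 − 0.21*q*) = 0.80(1 − 0.59*q*), so 0.325*q* = 0.10 and *q* ≈ 0.31.

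**Case C: no difference in other events, 5% in both groups.** Power is for a two-sided 0.05 comparison of two proportions with 60 per group (normal approximation).

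| *q* | Any event, QCHS v placebo | Power to declare QCHS superior on adverse events |
|---|---|---|
| 0.10 | 7.0% v 10.6% | about 10% |
| 0.25 | 10.0% v 19.0% | about 29% |
| 0.50 | 15.0% v 33.0% | about 64% |
| 1.00 | 25.0% v 61.1% | about 99% |

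**Weight of bleeding in the overall rate.** This is the share of placebo patients with any event who have a bleeding event. With other events at 5% it runs from 56% (*q* = 0.10) to 97% (*q* = 1). With other events at 20% it runs from 24% to 88%.

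**The case against.** The strongest reply is that no pooled adverse-event endpoint is defined. The Outcomes section lists none and the Statistical analysis section names no adverse-event test. Tabulation by type is commonly left to a SAP or full protocol, neither of which is shown. The safety objective is worded as exploratory, and the Discussion drops adverse effects from the hypothesis. This stands as a limit on the claim: the distortion arises only if events are compared overall. It does not remove the point, because the superiority hypothesis on side-effects and the unrestricted bloody-stools item are both stated in the text.

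A reader might infer that liver or renal harm would be hidden. The article does not support that. Liver and kidney tests are collected separately at the treatment visits, and the Termination criteria carry their own laboratory limits. Fewer bloody stools cannot change those values.

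A reader might also treat every non-responder as having a bleeding adverse event. That does not follow either. A patient can miss response on the total Mayo score or on another subscore, and bleeding unchanged from baseline need not be recorded as an event. For this reason *q* is varied and the extreme *q* = 1 should carry little weight.

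Finally, recording disease worsening as an adverse event is normal and is not criticised here. Dropping those events from the safety analysis would have its own cost: bleeding or colitis worsening caused by the product would disappear from view.

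**Conclusion.** The point holds in a limited form. A superiority hypothesis on adverse side-effects, together with an adverse event that overlaps the primary outcome, allows an overall comparison to tilt towards QCHS through efficacy alone. That tilt could partly or wholly offset an excess of other events. Under the assumptions above, a true 10% v 5% excess stays just visible at *q* = 0.10 and is reversed once *q* passes about 0.13; a 30% v 20% excess is reversed only beyond about 0.31.

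It would be tempting to conclude that the adverse-event result must largely repeat the efficacy result. The documents do not support this: bloody stools is one of seven example events, and its weight depends on recording and event rates that the article does not give. The conclusion also rests on the planning rates of 79% v 41% being realised, on independence of bleeding and other events, and on responders having no bleeding event recorded. A smaller efficacy difference, or bleeding events among responders at a similar rate, would reduce the tilt.

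**What to change.** 1. In Hypothesis and objective, take adverse side-effects out of the superiority list. State instead that the between-group difference in adverse events will be estimated, as a risk difference with a confidence interval. This also brings the section into line with the Discussion.
2. In Additional information, add a flag for UC-activity events such as bloody stools. Report adverse events by type, and overall both including and excluding the flagged events. Bleeding events stay in the full safety table.
3. State that no safety advantage will be claimed from the overall rate alone.

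This is a cheap improvement. It needs no new data: the cost is one coding flag, one additional table and giving up a superiority claim on side-effects. The article reports a blinded trial that was still enrolling, so the flag can be defined before the code is broken for analysis.
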